## Abstract

**Background:**

Population aging increases the need for knowledge on positive aspects of aging, and contributions of older people to their own wellbeing and that of others. We defined active aging as an individual’s striving for elements of wellbeing with activities as per their goals, abilities and opportunities. This study examines associations of health, health behaviors, health literacy and functional abilities, environmental and social support with active aging and wellbeing. We will develop and validate assessment methods for physical activity and physical resilience suitable for research on older people, and examine their associations with active aging and wellbeing. We will examine cohort effects on functional phenotypes underlying active aging and disability.

**Methods:**

For this population-based study, we plan to recruit 1000 participants aged 75, 80 or 85 years living in central Finland, by drawing personal details from the population register. Participants are interviewed on active aging, wellbeing, disability, environmental and social support, mobility, health behavior and health literacy. Physical activity and heart rate are monitored for 7 days with wearable sensors. Functional tests include hearing, vision, muscle strength, reaction time, exercise tolerance, mobility, and cognitive performance. Clinical examination by a nurse and physician includes an electrocardiogram, tests of blood pressure, orthostatic regulation, arterial stiffness, and lung function, as well as a review of chronic and acute conditions and prescribed medications. C-reactive protein, small blood count, cholesterol and vitamin D are analyzed from blood samples. Associations of factors potentially underlying active aging and wellbeing will be studied using multivariate methods. Cohort effects will be studied by comparing test results of physical and cognitive functioning with results of a cohort examined in 1989–90.

**Conclusions:**

The current study will renew research on positive gerontology through the novel approach to active aging and by suggesting new biomarkers of resilience and active aging. Therefore, high interdisciplinary impact is expected. This cross-sectional study will not provide knowledge on temporal order of events or causality, but an innovative cross-sectional dataset provides opportunities for emergence of novel creative hypotheses and theories.

## Background

In countries with aging populations, a key question regarding quality of life, sustainability, productivity, and equity of societies concerns whether old age is lived with functional limitations, disability and limited opportunities to contribute to the society, or whether it is spent with opportunities for participation and involvement in meaningful life situations. During the recent years, the idea of active aging has been essential in positive gerontology, in innovation programs and in policy. The concept of active aging stems from the work of Robert Havighurst who launched the activity theory [1]. The activity theory posits that staying active in later life will lead to maintenance of wellbeing. The contributions of older persons to their own wellbeing are of focal interest in many countries with growing proportion of older people in the population. Signaling this, World Health Organization defined the policy goal of active aging in 2002 as follows: “Active aging is the process of optimizing opportunities for health, participation and security in order to enhance quality of life as people age” [2]. The same document also states, “these policies and programs should be based on the rights, needs, preferences and capacities of older people”. The European Union programs such as the European Innovation Partnership on Active and Healthy Aging further demonstrate the importance of active aging in policy and innovation [3].

In gerontology, it is necessary to realize the distinction between active aging policies and active aging of individuals. Policies are goal-oriented actions of authorities while active aging in individual lives may not be categorized solely based on policy goals. Even though there has been a lot of attention on active aging, the empirical research and knowledge of active aging has progressed only little, and its definition and content have remained varied. To this end, we developed the following definition of active aging that is centered on the individual: “The striving for elements of wellbeing through activities relating to a person’s goals, functional capacities and opportunities” [4]. We developed a scale to assess active aging of individuals that is entitled the University of Jyvaskyla Active Aging Scale (UJACAS) [4]. This scale includes the four central sides in the active aging of individuals: their goals (what they want to do), their functional capacity (what they are able to do), their autonomy (perceived opportunities to do the valued activities) and their activities (what they actually do). We are not aiming to define active aging as a static position with clear-cut boundaries. Instead, we try to capture it as the striving for elements of wellbeing through activities relating to a person’s goals, functional capacities and opportunities.

Changes in self-reported disability, a reflection of an individual’s abilities relative to environmental requirements, do not necessarily reflect changes in the physical functioning of individuals but may result from changes in the environment. Muscle strength, reaction speed or sensory functions are the building blocks of functioning and active aging in terms that they underlie mobility (e.g. [5]), activities of daily living [5–7] and opportunities to take part in social life [8]. In Finland, the cohort comparisons among 65-year-old people suggest that socioeconomic situation has improved, physical activity is more common and self-ratings of health and functioning have improved but prevalence of chronic conditions has not changed [9]. Another study in Finland among 90-year-olds suggests that disability prevalence is increasing in oldest old cohorts [10]. However, among Danish nonagenarians cognitive functioning and activities of daily living functioning had improved [11]. In a Swedish study among 75-year-olds, gait speed had increased in later born cohorts, which was explained by taller body height in a more recent cohort [12].

Aging increases the risk of comorbidity and decline in the body functions and structures, which compromises the opportunities for active aging. Resilience refers to the ability to resist or recover from adverse effects of a stressor and it comes to play when a risk is present [13]. Earlier research has predominantly concentrated on social and psychological resilience and physiological indicators of resilience have been less studied. Physiological and psychological functions show great plasticity in old age and respond positively to training and rehabilitation and negatively to inactivity and disuse. Resilience is particularly salient for aging as the risk of stressors increases and the capacity to recover from them diminishes. Potential biomarkers of resilience are heart rate and heart rate variability since changes in heart rate reflect the function of the autonomic nervous system.

Active aging encompasses the idea that in case of functional limitations, active aging may be reached by compensating for the reduced abilities by environmental or social support. Addressing the person-environment interplay with objective technologies based on geographical maps and by recording physical activity and associated individual physiological responses under everyday living conditions and in standardized laboratory conditions with wearable sensors will provide novel knowledge on the person-environment interactions expanding knowledge that is based on reported perceptions of individuals. Social engagement refers to being part of a supportive social group and having various supportive resources, such as emotional, informational, finances or companionship. Social engagement is a resource for active aging.

Figure 1 shows the conceptual framework of the current study. The current study will further the research on active aging by addressing the individual and environmental factors relating to active aging and by assessing the benefits of active aging for the individuals. The current study will also produce new knowledge on whether the more recent cohorts of older people have better functional abilities than earlier cohorts.

**Fig. 1 Fig1:**
[figure not shown]
The conceptual framework of the current study. Active aging refers to the activity as per one’s goals, opportunities and abilities. It mediates or modulates the association of health and functioning with disability and wellbeing, while social engagement, environmental support and resilience influence this process, especially when facing adverse events

### Project aims

To examine health, health behaviors, health literacy and functional abilities as predictors of active aging.To examine if active aging supports wellbeing in old age (even) when facing functional decline.To examine how environmental support and social engagement influence active aging and wellbeing.To study the person-environment interactions underlying active aging and disability.To develop and validate objective assessment methods for physical activity suitable for research on older people, and examine their associations with active aging and wellbeing.To develop and validate biomarkers of physical resilience suitable for research on older people, and examine their associations with active aging and wellbeing.To study cohort effects on functional phenotypes that underlie active aging and disability.

## Methods

### Study design

AGNES is an observational study of three age cohorts (75, 80, and 85 years) with ongoing cross-sectional data collection (including phone and face-to-face interviews, postal questionnaire and assessments in a research center) and one-week activity surveillance with wearable monitors. In addition, the data will function as a baseline for an intervention study promoting active aging (trial registration number ISRCTN16172390) and it may function as a baseline for a future longitudinal study of the cohorts. The data collection is partly harmonized with a previous cohort study (Evergreen) including 75- and 80-year-old people assessed in 1989–1990 [14], thus providing an opportunity for cohort comparison.

### Sample size and power calculations

In the cross-sectional analysis for continuous variables a sample size of 1000 yields a power of approximately 99% to show a contribution to the explained variance of 5% in a linear regression model with 10 predictors (including interactions, but not constant) if the probability level (alpha) is set at 0.05. A sample size of 1000 yields weak correlation coefficients (*r* = 0.1) statistically significant. For cohort comparisons the sample size of 650 will give us 80% power to observe a 5% difference in continuous variables between the cohorts if the standard deviation is approximately a third of the mean as indicated by pilot data.

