### Contacting participants

Participants are invited to participate in the study by a letter informing them of the cohort study. Within a week a trained interviewer contacts them by phone to assess their willingness to participate. If they agree to participate, a home visit is scheduled and a reminder and a postal questionnaire are sent to them by mail. At the beginning of the home visit, the participant signs a written informed consent form. Following the home interview, participants are invited to participate in the physical activity surveillance (including an additional home visit to check and renew monitors) and the functional assessments in the research center. Figure 2 shows the approximate timeline of participant contacts.

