### Main outcomes

The main outcomes of this study are active aging and wellbeing and the secondary outcomes are resilience, physical activity, mobility, disability, environmental support and social engagement. For cohort comparisons, the main outcomes are physical, sensory and cognitive function, and the secondary outcome measures are wellbeing, health behavior, and physical activity.

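### The cohort-comparison power of 80% is about 77% on the stated inputs with 650 per cohort, and the protocol does not say what the 650 counts

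*Protocol article*

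**What the plan says.** Under Sample size and power calculations, the protocol article gives one sentence on the cohort comparison: "For cohort comparisons the sample size of 650 will give us 80% power to observe a 5% difference in continuous variables between the cohorts", on the condition "if the standard deviation is approximately a third of the mean as indicated by pilot data". An alpha of 0.05 appears earlier in the same paragraph, for the regression calculation. The cohort sentence gives no alpha, no sidedness and no second group size.

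Elsewhere the article sets the context:

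- **Study design** and **Discussion:** the comparison is with the 75- and 80-year-olds of a study carried out in 1989–1990. The size of that cohort is not given.
- **Recruitment process and inclusion criteria:** the target is 1000 participants over three ages, with no split by age.
- **Main outcomes:** "For cohort comparisons, the main outcomes are physical, sensory and cognitive function".
- **Table 1:** the objective tests of these functions that are also available in the historic cohort all carry code R (research center). They are chair-dynamometer strength, reaction time, maximal walking speed, visual acuity, spirometry, digit span, digit symbol and verbal fluency. Only self-reported hearing and vision come from the home interview.
- **Contacting participants:** "Following the home interview, participants are invited to participate in the physical activity surveillance". The same sentence covers the research-center assessments, so attendance there is a further step after the interview.

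**The concern.** A two-sample power statement needs a difference, a standard deviation, an alpha and two group sizes. Here the difference and the standard deviation are given, alpha has to be borrowed from a neighbouring sentence, and there is one group size whose meaning is not fixed. When the natural values are put in, the stated 80% does not come out.

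The project aim on cohort effects in functional phenotypes rests on this sentence. A finding of no cohort difference would be read against it, so readers need to know what power or detectable difference the design has, and for which count of people. The historic data are already collected, so that side of the comparison cannot be enlarged.

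**Working it through.** **Inputs**

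- Difference: 5% of the mean, so 0.05 in units of the mean (stated).
- Standard deviation: about 1/3 of the mean (stated as approximate).
- Alpha: 0.05, two-sided (assumed; 0.05 is stated only for the regression).
- Group sizes: 650, basis not stated. Equal cohorts are assumed first.

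**Standardized difference:** d = 0.05 / (1/3) = 0.15.

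**Attempt to reproduce 80%.** Power ≈ Φ(d·√(n/2) − 1.960), with n per cohort.

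- 650 per cohort: 0.15 × √325 = 2.704; 2.704 − 1.960 = 0.744; Φ = 77.2% (noncentral t: 77.1%).
- 650 in total, 325 per cohort: 0.15 × √162.5 = 1.912; 1.912 − 1.960 = −0.048; Φ = 48.1% (noncentral t: 48.0%).
- One-sided 0.05 does not give 80% either: 85.5% per cohort, 60.5% as a total.

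**What would give 80%**

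- Sample size: n = 2 × (1.960 + 0.842)² / 0.15² = 697.7, so about 700 per cohort.
- Standard deviation at 650 per cohort: 0.05 × √325 / 2.802 = 0.322 of the mean.
- Difference at 650 per cohort: (2.802 / 3) × √(2/650) = 5.2%. With 325 per cohort it is 7.3%.
- Unequal cohorts: 650 new participants against about 753 historic ones.

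**Sensitivity to the approximate standard deviation (650 per cohort, two-sided)**

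| SD / mean | Power |
|---|---|
| 0.32 | 80.4% |
| 0.325 | 79.2% |
| 0.33 | 78.0% |
| 1/3 | 77.2% |
| 0.34 | 75.5% |
| 0.35 | 73.1% |

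**Sensitivity to the number tested.** The article gives no attendance rate, so the rates below are assumptions. They apply only if 650 counts people interviewed. The historic cohort is held at 650, also an assumption. Power ≈ Φ(0.15 × √(n₁n₂/(n₁+n₂)) − 1.960).

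- 90% attendance, 585 vs 650: 0.15 × √307.9 = 2.632; Φ(0.672) = 74.9%.
- 80% attendance, 520 vs 650: 0.15 × √288.9 = 2.550; Φ(0.590) = 72.2%.

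**Sensitivity to the historic size.** With 650 new participants and an assumed historic cohort of 500, 600 or 800, power is 71.3%, 75.5% or 81.1%.

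**The case against.** The strongest reply is that the standard deviation is only approximately a third. At 0.32 of the mean, 650 per cohort gives 80.4%. Taking the standard deviation as a third of the lower mean gives 81.2%, and a log-scale analysis of a 5% decrease gives 81.3%. On this view 650 is a rounded but serviceable figure. That stands as far as it goes: 80% is reachable, and a reader should not infer that no reading supports it. But the same word covers 0.34 and 0.35, where power is 75.5% and 73.1%, and the value actually written gives 77%.

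A reader might infer that the true power is 48%. The article does not support this. It never calls 650 a total, and two of three ages out of 1000 would be about 667 if the ages were equal in size, so 650 fits the new cohort alone. The 48% shows only how much turns on the unstated basis.

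A reader might also take the loss at the research center as established. It is not. The article gives no attendance rate and does not say that 650 is counted before that step, so those figures stay conditional.

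The historic cohort's size may well be in the cited source, and an article can leave it there. Its absence alone is not an error. The difficulty is that a power figure is stated without showing that this size entered it.

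Finally, the neighbouring sentence beginning "A sample size of 1000 yields weak correlation coefficients" might look like a faulty power claim. It is true of an observed r of 0.1 at n = 1000 (t = 0.1 × √(998/0.99) ≈ 3.18) and claims no power, so it is not part of this point.

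**Conclusion.** The concern holds in a limited form. With the standard deviation at one third of the mean, two-sided alpha 0.05 and 650 in each cohort, power is 77%, not 80%. The gap is about 3 points, or a detectable difference of 5.2% instead of 5.0%. That alone would hardly change how a null result is read.

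The more useful part is that the sentence does not fix its own basis. It does not say whether 650 is per cohort, how many historic participants stand opposite, or whether 650 counts people interviewed or people tested. Any loss before the research-center tests, or a historic cohort below 650, lowers power further. How far cannot be told from the article; under the assumed 90% or 80% attendance it would be 75% or 72%. This is a correction of a stated figure and its description, not a defect in the design.

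**What to change.** Either of two changes would do.

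1. Restate the sentence: with 650 participants in each cohort, two-sided alpha 0.05 and a standard deviation of one third of the mean, the study has about 77% power for a 5% difference and 80% power for a 5.2% difference.
2. Preferably, recompute the power or the detectable difference from the actual number of historic participants with each test and the expected number of research-center attenders aged 75 and 80. State alpha and sidedness.

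In both cases, say whether the number is per cohort and whether it counts people tested. The cost is wording and a short recalculation. No participants are added, and under the first option the stated figure becomes slightly less favourable.

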### Recruitment process and inclusion criteria

The population register is used to target 75-, 80- and 85-year old people living in Jyväskylä, Finland, in postal areas within a 10 kilometer radius of the city center or within reach of local public transportation. The population-based study is targeted to include 1000 participants in total. Based on an estimated participation rate of 50% in previous studies, a sample of at least 2000 people would be needed. Participants aged 75 years old are recruited since September 2017, and in 2018, those aged 80 years and 85 years will be recruited. Samples are drawn from population registers shortly before the initiation of the assessment of each age-cohort. Inclusion criteria for the population-based study are age 75, 80 or 85 years, and living independently in the recruitment area (Jyväskylä). Exclusion criteria are unwillingness to participate and inability to communicate.

### Contacting participants

Participants are invited to participate in the study by a letter informing them of the cohort study. Within a week a trained interviewer contacts them by phone to assess their willingness to participate. If they agree to participate, a home visit is scheduled and a reminder and a postal questionnaire are sent to them by mail. At the beginning of the home visit, the participant signs a written informed consent form. Following the home interview, participants are invited to participate in the physical activity surveillance (including an additional home visit to check and renew monitors) and the functional assessments in the research center. Figure 2 shows the approximate timeline of participant contacts.

**Fig. 2 Fig2:**

Approximate timeline of participant contacts (indicated with vertical lines) and data collection from participants

### Data collection

#### Phone interview

During the initial phone interview, eligibility of potential participants is screened. A brief non-respondent interview is conducted, including five selected questions from the home interview on health and functioning. In addition, reasons for non-participation are asked from those who do not wish to participate in the study. If an individual agrees to participate, a time and date for the home interview is scheduled.

#### Postal questionnaire

Participants, for whom a home interview is scheduled, are asked to complete a questionnaire prior to the home interview. The interviewer returns the completed questionnaire to the research center or the participant brings the completed form to the research center at the time of the functional assessments.

#### Home interview

A face-to-face interview in the participants’ home is conducted by trained research staff to collect data on activity, health, functioning, and wellbeing. In addition, two short performance tests are conducted. Home interviews enable those with poorer health and function to participate.

#### Physical activity surveillance

Immediately following the home interview, participants are asked for their willingness to participate in the physical activity surveillance. Data on participants’ physical activity are collected using accelerometers and single-channel electrocardiogram (ECG) recorders. Participants are instructed to wear these devices day and night for 7 to 10 days, preferably until the assessments in the research center. While wearing these devices, participants complete a short diary on their daily activities. Halfway the assessment period, the interviewer renews the attachments and replaces the ECG recorder. Participants with a pacemaker are excluded from using an ECG recorder. As the activity monitors are not fully water-resistant, participants swimming, bathing or taking a sauna multiple times per week, and who are not willing to reduce these activities, are excluded from participation in the surveillance altogether.

#### Assessment in the research center

In the research center of the Faculty of Sport and Health Sciences of the University of Jyvaskyla, Finland, data are collected using a clinical examination, physical and cognitive performance tests, interviews, and physical activity monitors.

Participants receive written and verbal instructions for preparation of the assessments in the research center during the home interview. Participants are asked to refrain from extreme physical exertion, staying up late, and drinking alcohol on the day before the assessments, and not to consume caffeine containing drinks and not to smoke during the 2 h preceding the assessments. In addition, they are advised to consume only light meals on the day of the assessments, preferably no less than 2 h before arrival. Following the clinical examination and the anthropometric assessments, participants are provided with a light meal and drinks without caffeine.

